### Participants

A total of 180 FMS patients will be recruited from the Rheumatology service at Sant Joan de Déu Hospital (St. Boi de Llobregat, Spain). Sample size is established on the basis of a previous meta-analysis of controlled MBSR trials [45] in which a mean effect size of *d* = 0.53 was found. This effect size results in 1-b = 0.89 (alpha = 0.05) for *N* = 60 patients per group (180 patients overall). With 20 % maximal attrition, the power remains 1-b = 0.82. The estimated sample size for the study of biomarkers (neuroimaging and cytokines) was 30 participants per condition, this sample size is considered adequate given that approximately 20–40 participants (in between-group designs) are necessary to detect a change of 15 % in cerebral blood flow in regions of interest (ROI) by means of pseudo-continuous Arterial Spin Labeling (pCASL) [46].

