### Procedure

The potential FMS participants will be screened through an initial telephonic interview by one of the authors ([name]), who will provide a general overview of the study. Subsequently, two highly trained clinical psychologists (not involved with the treatment and blind to group allocation) will make an appointment with those patients who met the inclusion criteria and agreed to participate in the study. The psychologists will check all inclusion/exclusion criteria (both general and additional for the biomarkers study) and will perform all face-to face interviews. As mentioned above, study participants will be randomised to one of the three conditions (i.e., TAU, TAU + MBSR, TAU + FibroQoL). Both MBSR and FibroQoL are conducted in a group format (up to 15 people in each group). To balance the number of participants eligible for the biomarkers sub-study across the three arms, stratified randomisation will be performed. The proportion of eligible participants for the biomarkers evaluation and those only meeting criteria for the general study will be pre-fixed at 1:1 in all samples. Four treatment waves (*N* = 45 each) will be carried out to achieve the required final sample (*N* = 180).

Three-five days after the clinical evaluation, patients assigned to the biomarkers sub-study will be contacted for blood extraction and MRI completion. To minimise circadian variability in immunological markers, all whole blood samples will be collected between 8–9 am. Interventions will be conducted using a parallel design to reduce seasonal variability in the study measures. The participants will be interviewed at baseline, after treatment, and at 12-month follow-up (56 weeks after randomisation). The neuroimaging tests and cytokine measurements will be performed at baseline and after treatment. A flowchart of participants is displayed in Fig. 1.

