##### Brain function

Recent evidence [82] has demonstrated the suitability of pseudo-continuous arterial spin labeling (pCASL), a perfusion MRI technique, to quantify changes in regional cerebral blood flow (rCBF) that relate to the experience of ongoing persistent pain. In this study we will assess rCBF prior to and following the three treatments. pCASL data acquisition, pre-processing, and analysis methodologies have been published [82, 83], as applied to various disease states and therapeutic regimens, using gold-standard software packages (SPM-8 and FSL). We will acquire pCASL images using a gradient echo single shot echoplanar imaging readout resulting in whole-brain blood-flow maps. We will analyse pre-post rCBF differences within and between groups, and whether pre-post rCBF differences are related to variability in subjective ongoing pain.

Multiple resting-state networks have been found which show activity during rest and during tasks. One of them is the DMN, which shows a decrease in activity during cognitive tasks and is activated during self-referential thinking. Napadow et al. [12] showed that resting connectivity between the insular cortex (region involved in pain perception) and the DMN is significantly correlated with clinical pain at the time of the scan in FMS patients. In this work, we will use resting-state fMRI to compare changes in insular cortex-DMN connectivity between study conditions as well as to analysing any correlation between this connectivity and clinical pain. During the 8-min resting state fMRI acquisition period, the FMS patients will be instructed to remain awake with their eyes closed.

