#### Neuroimaging analyses

Treatment-related differences in both structural and functional MRI datasets will be assessed using mass-univariate voxelwise General Linear Models. Thus, repeated measures ANOVA functions available in SPSS will be computed to examine between- and within-group effects of treatments. A standard threshold of *p* < 0.05 will be applied for ROI data, correcting for multiple comparisons.

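### The between-arm imaging test should adjust for each patient's baseline value, and the claim that 30 per arm is adequate should be limited to pCASL blood flow

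*Protocol article*

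**What the plan says.** Under Participants, the protocol article states: "The estimated sample size for the study of biomarkers (neuroimaging and cytokines) was 30 participants per condition". One ground is offered for calling that number adequate, namely that "approximately 20–40 participants (in between-group designs) are necessary to detect a change". The size of change meant is 15 %, and the measure is regional blood flow by pCASL. No SD, power, sidedness or pre-post correlation is given for this sub-study, and the text does not say whether 20–40 is per group or in total.

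Under Procedure: "The neuroimaging tests and cytokine measurements will be performed at baseline and after treatment". There are therefore two measurements per patient.

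Under Brain function: "We will analyse pre-post rCBF differences within and between groups". Under Neuroimaging analyses, after naming voxelwise general linear models: "repeated measures ANOVA functions available in SPSS will be computed to examine between- and within-group effects of treatments". The 5 % threshold "will be applied for ROI data, correcting for multiple comparisons". No baseline covariate is mentioned. No between-arm model is stated for the cytokines.

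**The concern.** There are two separate points.

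**Precision.** In a repeated-measures ANOVA with two times, the treatment effect is the group-by-time term, which is the same test as comparing change scores between arms. It subtracts the baseline with a fixed coefficient of 1. A baseline-adjusted model estimates that coefficient from the data. In a randomised comparison it targets the same treatment effect with a variance that is never larger. The baseline scan is collected in any case, so the plan gives up precision it could have at no cost in patients or visits.

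**Scope of the adequacy claim.** The only support for 30 per arm is a figure for pCASL blood flow, yet the sentence covers neuroimaging in general and cytokines. IL-6, IL-8, IL-10 and CRP, and the morphometry, diffusion and connectivity measures, are different quantities with their own variability. The second study objective rests on these patients. Calling the sample adequate for all of these measures invites more confidence in a null result than the stated basis supports.

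**Working it through.** **Inputs.** From the protocol article: 30 per arm, a benchmark of 20–40 for a 15 % change, two measurement times, and analysis by repeated-measures ANOVA. Assumed, because the article does not state them: two-sided 5 %, 80 % power, 20–40 read as per group and as a single-measurement comparison, and equal variances at both times. Rho is unknown, so a range is shown.

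**The plan's own figure.** The 30 cannot be reproduced, because no SD or power is given. It can only be solved backwards with the normal formula d = (1.960 + 0.842) × √(2/n):
- n = 20 gives d = 0.886, so a 15 % difference implies a coefficient of variation of 15/0.886 = 16.9 %.
- n = 30 gives d = 0.723, coefficient of variation 20.7 %.
- n = 40 gives d = 0.626, coefficient of variation 23.9 %.

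**Variance of the treatment contrast.** Relative to comparing single post-treatment values (factor 1):
- change score (the group-by-time term): 2(1 − rho)
- baseline-adjusted: 1 − rho²
- ratio of adjusted to change: (1 − rho²) / [2(1 − rho)] = (1 + rho)/2

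The ratio is 0.65 at rho 0.3, 0.75 at rho 0.5 and 0.85 at rho 0.7: reductions of 35 %, 25 % and 15 %. It is below 1 for every rho below 1.

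**Power at 30 per arm** (normal approximation, one two-arm contrast, no multiplicity correction):

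| True need per group | rho | Post-treatment only | Change score | Baseline-adjusted |
|---|---|---|---|---|
| 20 | 0.3 | 0.929 | 0.826 | 0.949 |
| 20 | 0.5 | 0.929 | 0.929 | 0.977 |
| 20 | 0.7 | 0.929 | 0.993 | 0.998 |
| 30 | 0.3 | 0.800 | 0.658 | 0.836 |
| 30 | 0.5 | 0.800 | 0.800 | 0.899 |
| 30 | 0.7 | 0.800 | 0.951 | 0.975 |
| 40 | 0.3 | 0.679 | 0.536 | 0.720 |
| 40 | 0.5 | 0.679 | 0.679 | 0.800 |
| 40 | 0.7 | 0.679 | 0.879 | 0.925 |

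A simulation of 20,000 trials with a need of 30 agrees. Change against adjusted was 0.65 and 0.81 at rho 0.3, 0.79 and 0.88 at rho 0.5, and 0.95 and 0.97 at rho 0.7.

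The table shows two things. The adjusted column is above the change column in every row. The change column is below the post-treatment column only when rho is below 0.5, since 2(1 − rho) exceeds 1 only there.

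**How the gain shrinks.** With a need of 30, patients per arm for change against adjusted are 42 and 28 at rho 0.3, 30 and 23 at rho 0.5, 18 and 16 at rho 0.7, and 12 and 11 at rho 0.8.

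**What 30 per arm detects, for any outcome.** From the t distribution (slightly larger than the normal value of 0.723), a single unadjusted comparison at 80 % power and two-sided 5 % detects d = 0.736. With Bonferroni over three pairwise contrasts it is 0.857.

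**The case against.** The strongest reply is that the planned ANOVA is a valid test of the stated objective, which is pre-post change. It uses every baseline value, and covariates are often left to an analysis plan that is not shown here. The named general linear model does not exclude a baseline covariate. For longitudinal morphometry, change is itself the planned quantity. The imaging aims are also worded as exploration. All of this bears on how serious the point is. It does not remove it, because the article names the repeated-measures ANOVA and that choice is the less precise one. Nor does it force a change of estimand: change can stay the dependent variable, since adjusting change for baseline gives the same treatment contrast as adjusting the post-treatment value.

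A reader might go further and infer that 30 per arm is too small, or that the ANOVA loses power against the benchmark used for sizing. The documents do not support either:
- A loss against a single-measurement benchmark needs rho below 0.5, and no rho is given. At rho 0.7 the planned test does better than the benchmark comparison.
- The wording of the benchmark does not settle whether it concerns one measurement or change. If it already concerns change, there is no mismatch with the planned test.
- If 20–40 is a total, that is 10–20 per group, and 30 per arm exceeds even the upper end. If it is per group, 30 falls short only where the need is above 30.

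The objection is also right that Neuroimaging analyses covers MRI data only. There is no stated cytokine test to replace.

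**Conclusion.** The point holds as an available improvement in precision plus an adequacy claim that is too broad. It does not establish that the sub-study is undersized.

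The variance reduction of (1 − rho)/2 rests only on randomisation, two times and similar variance at each. It is 35 % at rho 0.3 and 15 % at rho 0.7, and becomes small as rho approaches 1. The power figures rest further on the assumed 80 % power, two-sided 5 % and the per-group, single-measurement reading. Baseline adjustment does not guarantee adequacy either: if the true need is 40 per group, it reaches 0.80 at 30 per arm only from about rho 0.5.

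That the pCASL figure does not cover cytokines or the other imaging measures depends on none of these assumptions. The component is secondary, and both corrections are changes of text.

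**What to change.** 1. **Neuroimaging analyses.** Make the between-arm test on ROI and voxelwise data a linear model of the post-treatment value (or of pre-post change) on arm, with the patient's own baseline value as covariate. Keep the within-arm pre-post results as description. If cytokines are compared between arms, state that the same model will be used.
2. **Participants.** Limit the word adequate to pCASL blood flow. Add that, at 80 % power and two-sided 5 %, 30 per arm detects d of about 0.74 in a single unadjusted comparison before multiplicity correction. Unless a separate calculation exists, say that none supports the size for cytokines or for the other imaging measures. Say also whether the 20–40 is per group, and give the SD and pre-post correlation if they are known.

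Cost: wording in two paragraphs, about one degree of freedom, and some set-up so that the voxelwise model accepts a covariate that differs by voxel. No new patients, visits or measurements are needed. The adequacy statement becomes more modest.

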### Eligibility criteria and Multi-stage recruitment process

For this study, we use a database with the medical records of FMS patients referred from local general practices to the Rheumatology Service at Parc Sanitari Sant Joan de Déu to confirm diagnosis. The sample pool consists of all FMS patients included in this database between January 2010 and September 2015 (N_sample pool_ = 531). Thus, all patients in the database were diagnosed with FMS (according to the American College of Rheumatology, ACR 1990 criteria) by rheumatologists from Parc Sanitari Sant Joan de Déu.

Patients meeting the following criteria will be eligible: 1. Patients of both genders between 18–65 years-old. 2. Able to understand the Spanish language. 3. Provide informed consent to participate. The following *general exclusion criteria* will be applied: 1. Participation in other RCTs. 2. Presence of cognitive impairment according to the Mini Mental State Examination (MMSE < 27). 3. Receiving psychological treatment during the previous or current year. 4. Reporting previous experience in meditation or other mind-body therapies. 5. Comorbidity with severe mental or medical disorders which interfere with treatment (severe medical illness, psychotic symptoms, substance abuse). 5. Unable to attend group sessions. 6. Pregnancy. 7. Involved in ongoing litigation relating to FMS.

Usual contraindications for scanning at 3Tesla and for measuring cytokine levels have been taken into account to establish the following additional inclusion/exclusion criteria for the biomarkers sub-study:*Inclusion criteria*: 1. Female gender. 2. Right-handed.*Exclusion criteria*: 1. Infection/cold symptoms on the day of blood extraction. 2. Needle phobia. 3. BMI > 36 kg/m^2^ or weight > 110Kg. 4. Neoplastic illnesses, infection, cardiopulmonary, vascular, or other internal conditions (collected from the medical history). 5. Use of oral or local corticosteroids or anticytokine therapy. 6. Consuming more than 7 caffeine units per day (1 caffeine drink will be permitted on the day of the study. 8. Smoking more than 5 cigarettes per day (no smoking will be permitted on the scanning visit days prior to scanning or whilst in the centre). 9. Cannot be evaluated by means of magnetic resonance imaging (MRI) (due to claustrophobia, metal implants, pace-makers, etc.). 10. Acute pain not -related to FMS on the day of the study (e.g. headache, lumbar pain). 11. Being pregnant or breastfeeding. It is important to point out that patients presenting neuroradiological alterations during MRI at baseline will be excluded from the sub-study. Patients will be allowed to continue with their stable medical treatment although, to reduce the effects of medications on biomarkers, they will be required to refrain from taking occasional (rescue) analgesic drugs (e.g., non-steroidal anti-inflammatory drugs, paracetamol) 72 h prior to the MRI and blood extraction. Changes in pharmacological/non-pharmacological treatment will be monitored throughout the study and may be a cause of drop-out from the final analyses.

### Procedure

The potential FMS participants will be screened through an initial telephonic interview by one of the authors ([name]), who will provide a general overview of the study. Subsequently, two highly trained clinical psychologists (not involved with the treatment and blind to group allocation) will make an appointment with those patients who met the inclusion criteria and agreed to participate in the study. The psychologists will check all inclusion/exclusion criteria (both general and additional for the biomarkers study) and will perform all face-to face interviews. As mentioned above, study participants will be randomised to one of the three conditions (i.e., TAU, TAU + MBSR, TAU + FibroQoL). Both MBSR and FibroQoL are conducted in a group format (up to 15 people in each group). To balance the number of participants eligible for the biomarkers sub-study across the three arms, stratified randomisation will be performed. The proportion of eligible participants for the biomarkers evaluation and those only meeting criteria for the general study will be pre-fixed at 1:1 in all samples. Four treatment waves (*N* = 45 each) will be carried out to achieve the required final sample (*N* = 180).

Three-five days after the clinical evaluation, patients assigned to the biomarkers sub-study will be contacted for blood extraction and MRI completion. To minimise circadian variability in immunological markers, all whole blood samples will be collected between 8–9 am. Interventions will be conducted using a parallel design to reduce seasonal variability in the study measures. The participants will be interviewed at baseline, after treatment, and at 12-month follow-up (56 weeks after randomisation). The neuroimaging tests and cytokine measurements will be performed at baseline and after treatment. A flowchart of participants is displayed in Fig. 1.

